### Participants

Suitable participants will be screened at each center for their eligibility to participate in the study:

The inclusion criteria are as follows: (1) females over 18 years of age; (2) first and second-year undergraduate students; (3) no vaccination contraindications; (4) having mobile phone or computer access.

The exclusion criteria are as follows: (1) males; (2) females under 18; (3) non-undergraduate first or second-year students; (4) medical students; (5) previous history of vaccination contraindications; (6) current pregnancy or breast feeding.

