**Methods:**

This investigation is a multicenter, school-based, prospective, randomized, parallel group, double-blind, blank-controlled trial involving a 7-day education intervention with a further 6-month follow-up. We will enroll at least 3360 participants older than 18 years. The enrolled participants will be randomly divided into two groups (1:1 ratio). The intervention group will be offered a 7-day mobile health education, and participants in both groups will fill out 4 questionnaires at the baseline, 1 month, 3 months and 6 months after the intervention. The primary outcome is the difference in HPV vaccination or reservation for the HPV vaccine between the intervention and control groups. Secondary outcomes will include the comparison of (1) knowledge, attitudes, motivation, beliefs and behavioral skill about HPV and cervical cancer prevention, and (2) the willingness to uptake HPV vaccination.

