### Sampling and randomization

The study process consists of the following four phases:

Phase 1: Confirm the stratified sampling framework by geographical territories of China.

The stratified sampling of the 31 provinces/municipalities/autonomous regions in China is conducted from seven geographical territories, namely East China, South China, Central China, North China, Northwest China, Southwest China and Northeast China.

Phase 2: Convenient sampling to determine the cities and universities to be included within the geographic territories in Phase 1.

We select a representative city in each of the seven geographical territories using the convenient sampling method. A total of 7 cities (Jinan of Shandong Province, Guangzhou of Guangdong Province, Zhengzhou of Henan Province, Beijing, Urumqi of Xinjiang Uygur Autonomous Region, Chengdu of Sichuan Province, Dalian of Liaoning Province) were finally decided to be the study sites. In each representative city, a comprehensive university is selected. A total of 7 universities (Shandong University, Zhongshan University, Zhengzhou University, Capital Normal University, Xinjiang University, Sichuan University, Dalian University of Technology) are finally confirmed as research centers for this study.

Phase 3: Cluster sampling in each of the seven research centers.

After satisfying the inclusion criteria, at least 240 university students will be selected by class from the literature and science majors (excluding medical majors) respectively, and a total of 480 samples will be composed at each of the seven centers. This selection will result in a total of at least 3360 participants across 7 schools.

Phase 4: Randomization and allocation in each center.

After the baseline survey, all identified participants will be randomly assigned to the intervention group or control group in a 1:1 ratio, and each group at each center will have 240 participants. Randomization will be stratified with regards to majors, resulting in two separate categories of literature and science majors. The random sequence will be generated using SAS V.12. (SAS Institute) software. Furthermore, randomization will be conducted by personnel not involved in the trial at each of the seven universities.

After randomization, the researcher who assigns participants to the intervention will provide information about the mobile-based education. This researcher will no longer be blinded from this point.

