#### Baseline

Prior to the intervention, the baseline survey will be conducted to assess socio-demographic and HPV vaccination status, sexual history, and knowledge, attitudes and beliefs about HPV and HPV vaccination.

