#### Outcome measures

Our primary outcomes of interest will be the difference between the intervention and the control group, which include: (1) knowledge, attitudes and beliefs about HPV, cervical cancer and the HPV vaccine; (2) intent to uptake the HPV vaccine; and (3) the reception of or an appointment for the first dose of the HPV vaccine.

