#### Baseline measures

We will collect participants’ HPV vaccination status, socio-demographic information (date of birth, nationality, religion, habitual residence, economic status, parental employment and marital status, and family or friends’ cancer history), health and sexual history. We will also record information about knowledge, cognition and beliefs related to HPV and HPV vaccination, motivations and intentions to uptake the HPV vaccine, decision-making, self-efficacy and objective skills regarding HPV vaccination. For background information, we will refer to the relevant part of several related studies conducted in China previously. The 11-item scale from Kahn JA and the HAVIQ (HPV Adolescent Vaccine Intervention Questionnaire) from Forster AS will be partly used to measure knowledge about HPV and HPV vaccination [30, 31]. For measuring cognition of HPV infection and prevention, we will use scales from Kim HW, Gerend MA and Guvenc G [32–34]. This will assess the perceived severity of HPV infection and the perceived benefits and barriers of HPV vaccination. Two scales from Ralph will be used to measure the perceived susceptibility of HPV infection [35]. The 5-item scale from Gerend MA will be adopted to test the influence of subjective norms [33]. For measuring decision-making for health protection, we will use the 3-item scale of Forster AS [31]. Self-efficacy for completing the 3-dose HPV vaccination will be tested using the 4-item scale of Gerend MA [33]. The self-administered 4-item scale developed by Fisher will also be used to measure the objective skills needed to initiate and complete HPV vaccination [26]. Finally, intent to receive the HPV vaccine will be measured according to the answer to the question: “Willingness to take the HPV vaccine in the next 6 months”.

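### Women already vaccinated or booked at baseline stay in a comparison of first doses, which dilutes the effect estimate and leaves its meaning unclear

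*Protocol article*

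**What the plan says.** All references are to the protocol article.

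- **Participants.** The inclusion list ends with "3) no vaccination contraindications; (4) having mobile phone or computer access" and the exclusion list with "4) medical students; (5) previous history of vaccination contraindications; (6) current pregnancy or breast feeding". Both lists appear complete. The items on contraindications do not cover earlier HPV vaccination, and nothing else in either list does.
- **Baseline and Baseline measures.** Before the intervention, "the baseline survey will be conducted to assess socio-demographic and HPV vaccination status".
- **Sampling and randomization.** "After the baseline survey, all identified participants will be randomly assigned to the intervention group or control group in a 1:1 ratio". Stratification is by major only; baseline vaccination status has no role in it.
- **Outcome.** In the Abstract (Methods), "The primary outcome is the difference in HPV vaccination or reservation for the HPV vaccine between the intervention and control groups". Outcome measures narrows this to "the reception of or an appointment for the first dose of the HPV vaccine".
- **Sample size calculation.** The assumed rates, 20% v 10%, are for girls who start vaccination.
- **Statistical analysis.** The analysis is by intention to treat. Proportions are compared by chi-squared test at baseline and at 1, 3 and 6 months, change from baseline is tested within groups by McNemar's test, and odds ratios come from logistic regression. No restriction to women unvaccinated at entry is stated.

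**The concern.** A woman who has had her first dose, or has already booked it, cannot have the primary event because of the intervention. Some such women are to be expected. The Background says the vaccines reached mainland China between 2016 and 2018, Study setting gives a start in November 2019, and the plan itself measures vaccination status at baseline.

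The plan keeps these women in the comparison without saying how they are counted. If the outcome is status at follow-up (ever vaccinated or booked), they are successes in both arms. If it is a new first dose or booking during follow-up, they are failures in both arms. Either way they carry no information on the effect and shrink the absolute difference. The two codings can give clearly different odds ratios from the same data, and the odds ratio with its 95% CI is the effect measure that the plan will report.

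**Working it through.** **Inputs.** Rates of 20% v 10%, two-sided α = 0.05, β = 0.20, 20% loss, and 240 per group per centre (Sample size calculation). Seven centres give 7 × 240 = 1680 per arm. After 20% loss, 240 × 0.8 = 192 per group per centre and 1680 × 0.8 = 1344 per arm overall. The share already vaccinated or booked, v, is **an assumption**: the Discussion says that exact baseline vaccination data are lacking.

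**The plan's own figure.** With pooled variance, n = [1.960·√(2·0.15·0.85) + 0.842·√(0.20·0.80 + 0.10·0.90)]² / 0.10² = (0.990 + 0.421)² / 0.01 ≈ 199 per group. The article prints 119. No variant tried (continuity-corrected, unpooled, arcsine, one-sided) gives 119, whereas 199 × 1.2 ≈ 239 is close to the stated 240. The 119 therefore looks like a misprint of 199. That is a separate matter; the enrolment of 240 per group is used below.

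**Effect of v.** The 20% v 10% rates are applied only to the (1-v) women still at risk.

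- Counted as successes: v + (1-v)·0.20 against v + (1-v)·0.10.
- Counted as non-responders: (1-v)·0.20 against (1-v)·0.10.
- Under both, the risk difference is (1-v)·0.10.

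Example, v = 10%. As successes: 0.10 + 0.9·0.20 = 28% against 0.10 + 0.9·0.10 = 19%, so OR = (0.28/0.72)/(0.19/0.81) = 1.66. As non-responders: 18% against 9%, so OR = (0.18/0.82)/(0.09/0.91) = 2.22.

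| v | Risk difference (points) | As successes: rates, OR | As non-responders: rates, OR |
|---|---|---|---|
| 0% | 10.0 | 20.0% v 10.0%, 2.25 | 20.0% v 10.0%, 2.25 |
| 2% | 9.8 | 21.6% v 11.8%, 2.06 | 19.6% v 9.8%, 2.24 |
| 5% | 9.5 | 24.0% v 14.5%, 1.86 | 19.0% v 9.5%, 2.23 |
| 10% | 9.0 | 28.0% v 19.0%, 1.66 | 18.0% v 9.0%, 2.22 |
| 20% | 8.0 | 36.0% v 28.0%, 1.45 | 16.0% v 8.0%, 2.19 |

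**Power** (pooled-variance test).

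| v | Successes, one centre (192 per group) | Non-responders, one centre | At-risk women only, one centre (192(1-v)) | Successes, seven centres (1344 per arm) |
|---|---|---|---|---|
| 0% | 79% | 79% | 79% | >99.9% |
| 5% | 66% | 76% | 77% | >99.9% |
| 10% | 55% | 73% | 74% | >99.9% |
| 20% | 39% | 68% | 69% | 99.4% |
| 30% | 29% | 61% | 63% | 96% |

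In the restricted set the expected odds ratio is 2.25 and the risk difference 10 points, whatever v is.

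**The case against.** Four points can be made for the plan.

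**The outcome may already mean a new event.** It names the first dose, and Follow-up measures asks for reasons from women who did not receive or order a dose during the trial. On that reading the odds ratio hardly moves, and restricting the analysis gains only one or two points of per-centre power. This is a fair reading, but not a settled one. The repeated chi-squared tests, which include baseline, and the McNemar tests against baseline fit a status outcome just as well. Even on the new-event reading the risk difference is diluted.

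**A reader might infer that the trial loses its power.** The falls to 66%, 55% and 39% apply only within a single centre, which is how Sample size calculation derives n. The Abstract's primary comparison is intervention against control overall, and Statistical analysis specifies no per-centre test. The pooled comparison remains well powered. A larger sample does not remove the dilution, however; it only makes the diluted estimate more precise.

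**A reader might infer bias between the arms.** Randomisation follows the baseline survey, so these women are balanced in expectation. The chance difference in their share has a standard deviation of √(2·0.05·0.95/1680) ≈ 0.75 points at v = 5% and about 1.0 point at v = 10%, and the ordinary standard error already reflects it.

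**The plan has ways to cope, and a reason to enrol everyone.** Baseline status is recorded and a multivariable logistic model is planned. Recruitment by class and the objective of identifying factors that influence vaccination both favour enrolling all comers. This argues against requiring an exclusion criterion. It does not settle the primary comparison: the model's covariates are unnamed, and the chi-squared tests and unadjusted odds ratio would still include these women. Nor is this merely detail left to an analysis plan, because the article itself sets a full eligibility list, randomises everyone and commits to intention to treat.

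**Conclusion.** The point holds as a should-fix. As written, the plan puts women who can no longer start vaccination into a comparison of starting vaccination, and does not say how they count. The risk difference is diluted to (1-v) × 10 points under either coding. The odds ratio falls to between 2.06 and 1.45 for v from 2% to 20% if they count as successes, and stays at about 2.2 if they count as non-responders.

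These sizes rest on an assumed v and on the plan's 20% v 10% holding among women still at risk. The Background describes vaccination rates as low and the vaccine as self-paid, and v = 20% would be twice the plan's own control-arm rate, so the lower part of the range is easier to reconcile with the article. The documents do not support a claim of systematic bias, of an underpowered pooled comparison, or that such women must be barred from enrolling.

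**What to change.** Define the primary analysis set for the vaccination outcome as all randomised women with no HPV dose and no appointment for one at the baseline survey, analysed in the arm to which they were assigned. State that the event is a first dose or appointment arising after randomisation. Keep the full randomised set as a sensitivity analysis, with the coding of women positive at baseline stated, and for the secondary objectives. Settle this before outcome data are seen, so that no choice between codings is made afterwards.

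Because status is recorded before randomisation, the restricted comparison remains a randomised one. The cost is one analysis-set sentence and a denominator smaller by the fraction v: at v = 10%, 1344 × 0.9 ≈ 1210 per arm after loss. Baseline measures names vaccination status but does not mention bookings, so the questionnaire should be checked for an item on existing appointments and one added if it is absent. A new exclusion criterion would also work but is optional.

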### Recruitment and informed consent

All enrolled participants will be informed of the research objectives, the study procedures, their rights and obligations, the expected benefits and the possible risks to the participants before they sign the informed consents (Appendix). Participants in the study will also have the right to freely obtain more information at any time and will be allowed to freely withdraw from the study without restrictions at any research stage.

Once each participant signs the informed consent, the researchers will complete the eligibility checklists and records will be made of any candidate who fails to meet the inclusion criteria. Additionally, in order to facilitate follow-up services, we need participants to leave a mobile phone number or WeChat account. All of the above information is stored on an encrypted laptop and kept by a dedicated person with strict information confidentiality.

### Sampling and randomization

The study process consists of the following four phases:

Phase 1: Confirm the stratified sampling framework by geographical territories of China.

The stratified sampling of the 31 provinces/municipalities/autonomous regions in China is conducted from seven geographical territories, namely East China, South China, Central China, North China, Northwest China, Southwest China and Northeast China.

Phase 2: Convenient sampling to determine the cities and universities to be included within the geographic territories in Phase 1.

We select a representative city in each of the seven geographical territories using the convenient sampling method. A total of 7 cities (Jinan of Shandong Province, Guangzhou of Guangdong Province, Zhengzhou of Henan Province, Beijing, Urumqi of Xinjiang Uygur Autonomous Region, Chengdu of Sichuan Province, Dalian of Liaoning Province) were finally decided to be the study sites. In each representative city, a comprehensive university is selected. A total of 7 universities (Shandong University, Zhongshan University, Zhengzhou University, Capital Normal University, Xinjiang University, Sichuan University, Dalian University of Technology) are finally confirmed as research centers for this study.

Phase 3: Cluster sampling in each of the seven research centers.

After satisfying the inclusion criteria, at least 240 university students will be selected by class from the literature and science majors (excluding medical majors) respectively, and a total of 480 samples will be composed at each of the seven centers. This selection will result in a total of at least 3360 participants across 7 schools.

Phase 4: Randomization and allocation in each center.

After the baseline survey, all identified participants will be randomly assigned to the intervention group or control group in a 1:1 ratio, and each group at each center will have 240 participants. Randomization will be stratified with regards to majors, resulting in two separate categories of literature and science majors. The random sequence will be generated using SAS V.12. (SAS Institute) software. Furthermore, randomization will be conducted by personnel not involved in the trial at each of the seven universities.

After randomization, the researcher who assigns participants to the intervention will provide information about the mobile-based education. This researcher will no longer be blinded from this point.

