The mobile health intervention contains a high level of interactivity. Participants will be allowed to engage in mutual conversation amongst themselves on different topics of intervention. Based on the mobile application, the intervention group and the control group at each center will establish a chat group respectively, and the administrator will automatically upload 10 min of educational content in the intervention chat group only. After completing the learning session, participants can perform punching and talk about the educational content.

Control group(no intervention/ black control).

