#### Intervention procedure

Upon completion of the baseline assessment, two research staff will anonymize and number the students. The staff will then randomize participants to either the intervention group or control group. The intervention and control group will have at least 240 participants respectively at each of the seven centers. Timing randomization in this way ensures we can balance intervention and control groups on baseline characteristics. One unblinded research staff will remain in contact with participants via the mobile app. The intervention group will receive digital education materials every day during the 7-day intervention period, while the control group will not have any form of intervention. Possible intervention non-attendance and trial non-compliance will be collected and followed up via telephone by the unblinded researcher.

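### Students are sampled by class but randomised individually, so most controls will have classmates in the intervention arm, and any sharing of the lessons would dilute the measured effect

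*Protocol article*

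**What the plan says.** All references are to the protocol article.

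- **Sampling unit.** Sampling and randomization has the heading "Phase 3: Cluster sampling in each of the seven research centers". Under it, "at least 240 university students will be selected by class from the literature and science majors", giving 480 students per centre.
- **Randomisation unit.** Phase 4 of the same section says that "all identified participants will be randomly assigned to the intervention group or control group in a 1:1 ratio". Intervention procedure confirms that the unit is the student: "two research staff will anonymize and number the students. The staff will then randomize participants to either the intervention group or control group".
- **Strata.** "Randomization will be stratified with regards to majors", carried out within each centre. Class is neither a unit of allocation nor a stratum.
- **Content and delivery.** Interventions describes seven daily digital sessions for phone or computer, which include where the vaccine can be had locally and what it costs. Each arm has its own chat group at each centre, and "the administrator will automatically upload 10 min of educational content in the intervention chat group only". Discussion is part of the design: "Participants will be allowed to engage in mutual conversation amongst themselves on different topics of intervention".
- **Comparator.** Intervention procedure says the intervention group receives the materials daily, "while the control group will not have any form of intervention". Follow-up runs to 6 months.
- **Blinding.** Participants are to be told their allocation only after the final assessment (Blinding).

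**The concern.** Sampling by class brings classmates into the trial together, and individual allocation then places them in different arms. The material is short, digital and meant to be talked about, and some of it (a peer's story, local availability, price) can be passed on in a sentence. Separate chat groups control where the lessons are posted. They do not control what a student shows or tells the person in the next seat.

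If the education works, any transfer raises the outcome in controls and biases the difference towards zero. This applies to vaccination or booking and also to knowledge, attitudes and intent, which Outcome measures lists beside uptake. A modest result could then mean either that the education has a modest effect or that some controls received it too. Neither the sample size section nor the limitations in the Discussion mentions the possibility.

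**Working it through.** **Inputs from the protocol article.** 20% v 10%, two-sided α = 0.05, 80% power, 20% loss, 240 per group per centre, 7 centres (Sample size calculation); 240 students per major category per centre, allocated 1:1 (Sampling and randomization).

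**Assumed.** Enrolled students per class (m), the fraction of controls receiving the full effect (c) and the intraclass correlation (ICC). The article gives none of these.

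**The plan's own figure.** The pooled-variance formula for 20% v 10% is

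n = [1.96√(2 × 0.15 × 0.85) + 0.8416√(0.16 + 0.09)]² / 0.10² = 199 per group.

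The stated 119 does not reproduce; its power is about 58%. The stated 240 fits 199 × 1.2 = 239. This is a separate matter, and nothing below depends on it.

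**Step 1: does a control have intervention classmates?** Take a stratum of 240 with 120 per arm. For a control in a class with m enrolled students, the probability that none of the other m − 1 is in the intervention arm is the product of (119 − i)/(239 − i) for i = 0 to m − 2.

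| m | P(at least one intervention classmate) | expected number |
|---|---|---|
| 5 | 94.0% | 2.0 |
| 8 | 99.3% | 3.5 |
| 10 | 99.8% | 4.5 |
| 20 | about 100% | 9.5 |

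This is the opportunity for transfer, not transfer itself.

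**Step 2: effect of transfer on the contrast and on power.** Control rate = 0.10 + 0.10c. Odds ratio = 0.25 / [rate/(1 − rate)]. The pooled number per arm after loss is 7 × 240 × 0.8 = 1344; per centre it is 240 × 0.8 = 192. With difference d and mean rate p̄,

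power = Φ{[d√n − 1.96√(2p̄(1 − p̄))] / √(p₁(1 − p₁) + p₂(1 − p₂))}.

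| c | control rate | difference (points) | OR | pooled power (1344) | per-centre power (192) |
|---|---|---|---|---|---|
| 0 | 10% | 10 | 2.25 | >99% | 78.6% |
| 20% | 12% | 8 | 1.83 | >99% | 57.1% |
| 30% | 13% | 7 | 1.67 | >99% | 45.5% |
| 50% | 15% | 5 | 1.42 | 92.7% | 25.1% |

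For c = 50%, pooled: (0.05 × 36.66 − 1.96 × 0.537)/0.536 = 1.45, and Φ(1.45) = 0.927. Pooled power falls below 80% at c of about 59%.

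**Step 3: the alternative of allocating whole classes.** Design effect = 1 + (m − 1) × ICC. With m = 30 and ICC 0.05 it is 1 + 29 × 0.05 = 2.45.

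- Pooled: 1344/2.45 = 549 effective per arm, power above 99%.
- Per centre: 192/2.45 = 78 effective per arm, power about 42%.

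With ICC 0.10 the design effect is 3.9. That leaves about 345 effective per arm pooled (96%) and 49 per centre (28%).

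**The case against.** The strongest reply is that the article shows opportunity, not leakage. Class sizes, daily contact between classmates and every value of c are assumptions. A forwarded lesson is also less than seven daily sessions with attendance records and group discussion, so full-effect transfer is a severe assumption. The arms have separate chat groups, and the talk that the article invites belongs to the intervention; it does not encourage conversation across arms. All of this stands, and it is why the size can be given only as a range.

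A reader might go further in four directions that the document does not support:

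- **That the trial loses its power.** It does not, at the planned effect: pooled power holds to about c = 59%. A null pooled result would need very heavy contamination or a true effect well below the planned one.
- **That exposure of controls goes unmeasured.** The follow-up sections list domains in a condensed article, and the questionnaires are not shown. The absence of an exposure item cannot be asserted.
- **That the intention-to-treat difference is a lower bound on the true effect.** Contamination alone would attenuate it, but differential loss or self-reported vaccination could push it upwards.
- **That individual allocation is an error.** Choosing between individual and class allocation trades contamination against clustering. Class allocation would also leave students of the same major and university in both arms, so it would reduce sharing without ending it.

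**Conclusion.** The point holds as a risk of attenuation created by the design. It is certain from the text that students are sampled by class and allocated individually, and that the only separation described is where the content is posted. It is very probable, for about 5 or more enrolled students per class, that a control has at least one intervention classmate. How much would pass between them is unknown.

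If 20% to 50% of controls received the full effect, a true 10-point difference would be measured as 8 to 5 points. The main harm is to the estimate and its interpretation, not to the pooled test. Comparisons within a single centre, the level at which the article sizes the study, are more fragile: power there starts at 78.6% after loss and is 57.1% at c = 20%. This is worth correcting before randomisation because the correction is cheap, but it does not invalidate the design.

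**What to change.** **Main change.**

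1. At the start of the 7 days, instruct intervention participants not to forward or show the lessons outside their chat group until the 6-month assessment is complete.
2. Unless such items already exist, add to the 6-month questionnaire in both arms, after all outcome items, neutrally worded questions on whether the participant saw or was shown app-based HPV lessons during the study and on roughly how many days. In the intervention arm, also ask whether she shared them. Placing these last, and only at 6 months, avoids prompting controls or disclosing allocation before the outcomes are recorded.
3. Report the exposed share of controls beside the intention-to-treat result and state that contamination would attenuate that result, without calling it a lower bound.

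Cost: one instruction and a slightly longer final questionnaire, with no extra participants. Exposure will be self-reported and recalled over six months.

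**Alternative to consider.** Allocate whole classes 1:1 within centre and major, and account for class in the analysis. Under the assumptions in Step 3 the pooled comparison remains well powered, but per-centre power falls to about 42%. Sponsors who want centre-level conclusions would pay heavily for it.
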